## **5.2.6 Subject screening and recruitment**

Teachers at each rehabilitation institution will assist in disseminating recruitment information to potential participants via text messages posted in school-affiliated WeChat groups. Parents who express interest will be invited to complete an online screening survey by

scanning a QR code provided on the recruitment information sheet. The screening will include questions (e.g., the child's age, respondent's daily caregiving hours) to assess eligibility against the study criteria. Following identification of potentially eligible parents, research assistants will contact them by telephone to introduce the study, assess interest, and schedule an in-person meeting. At the in-person meeting, research assistants will explain the study objectives, procedures, potential benefits and risks, and participants' rights (including the option to withdraw at any time). Written informed consent will be obtained after parents indicate full understanding and all questions have been addressed.

#### **5.2.7 Randomization and concealment**

Eligible participants will be randomly assigned in a 1:1 ratio to either an ACT-based parenting program plus usual care (intervention group) or usual care only (control group), using permuted block randomization with variable block sizes of four or six. The allocation sequence will be generated by an online randomization program and administered by a research assistant (a registered nurse with a master's degree in nursing) who will not be involved in participant recruitment, intervention delivery, or outcome assessment. Group allocation will be concealed from outcome assessors, rehabilitation school teachers, parents, and children using sequentially numbered, opaque, sealed envelopes.

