#### **5.2.4 Settings and Subjects**

Parents will be recruited through seven rehabilitation institutions for children with developmental disabilities or delays in Guangdong Province, China. All seven institutions are located in urban districts of Shenzhen—a highly developed metropolitan area—and share comparable characteristics in organizational structure, funding support, service offerings, professional qualifications, and staff composition, representing services commonly provided by non-governmental institutions to children with ASD and their families in mainland China. Each institution is a privately operated, designated rehabilitation service provider authorized by the Shenzhen Disabled Persons' Federation and operates in accordance with government regulations. Under Shenzhen municipal policies for rehabilitation assistance for children with disabilities, intervention costs at these institutions can be subsidized by the government up to 50,000 RMB (approximately 7,021 USD) per child per year. The institutions included: Shenzhen Xinkangle Special Education and Rehabilitation Institution, Shenzhen Xingxinyuan Special Education and Rehabilitation Institution, Shenzhen Bougainvillea Special Needs Children's Rehabilitation Institution, Shenzhen Happy Nut Special Needs Children's Rehabilitation Institution, Shenzhen Love Ear Tree Special Needs Children's Rehabilitation Institution, Shenzhen Wishing Tree Special Needs Children's Rehabilitation Institution, and Shenzhen Stars Special Needs Children's Rehabilitation Institution. The first four sessions of

the intervention were administrated face-to-face at the children's rehabilitation institutions, and the last four sessions were conducted through an online videoconferencing platform (Tencent Meeting).

Participants (Parents) will be eligible if they are: (1) aged  $\geq 18$  years old; (2) parent of children aged between 3 to 9 years diagnosed with autism; (3) primary family caregivers responsible for daily care of their children with autism; (4) able to communicate and understand Mandarin; and (5) able to complete online sessions and questionnaires through mobile phone or computer.

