#### **5.2.8 Intervention Group**

In addition to usual care, parents in the intervention group will receive eight weekly sessions (2 hours per session) of an Acceptance and Commitment Therapy (ACT)-based parenting program delivered by the research team. The program will be administered in a

blended group format (face to face and online), with approximately 6–8 participants per group. The curriculum will cover four domains: (1) emotional and stress management (ACT); (2) autism-specific parenting skills; (3) autism-related education; and (4) self-care.

To establish rapport between the facilitator and participants, Session 1 will be delivered face to face. Sessions 2–4 will also be delivered face to face because they include experiential exercises (e.g., role-playing, mindfulness practices) that support learning of complex techniques and concepts. Sessions 5–8 will be delivered via an online videoconferencing platform (Tencent Meeting). During the final four online sessions, parenting practices will be taught step by step using instructional parenting videos, and core ACT principles (e.g., self-as-context) will be introduced using animated metaphor videos. All videos will be drawn from trustworthy, validated sources recommended by the World Health Organization’s Caregiver Skills Training for Families of Children with Developmental Delays and Disabilities (WHO-CST) and/or ACT manuals. Parents will receive a workbook outlining core ACT principles, key parenting skills, and weekly homework. Participants will be able to access online mindfulness practice videos after class by scanning QR codes provided in the workbook. A session-by-session outline of the ACT program will be provided in Table 1.

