### **5.2.9 Control Group**

Based on the government policy document titled “Management Measures for Designated Rehabilitation Service Institutions for Disabled Children and Youth in Shenzhen”, parents will receive usual care services from their children’s rehabilitation institutions delivered by institutional staff (rehabilitation therapists, special educators, social workers with standard

local credentials) as part of routine, year-round services. To minimize nonspecific influences, both groups will have access to institution-based staff with comparable professional credentials and opportunities for contact and information provision. Usual care services will comprise in-person group education (~1 to 2 hours/session) and outreach activity (~3 to 4 hours/activity) held at least twice annually, as well as ad hoc individual consultations (~15 to 30 minutes/visit) covering autism-related rehabilitation education, interpretation of government support policies, or education on parental/child psychological health, with crisis referral when indicated). Usual care services will not include structured ACT content or the manualized WHO-CST curriculum; any overlap will be limited to general psychoeducation without skills training or fidelity-monitored components.

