#### **5.2.11 Data collection procedure**

Primary and secondary outcomes will be assessed at baseline (T0), immediately post-intervention (T1), and six months post-intervention (T2). All quantitative data will be collected via an online questionnaire platform (WJX.com) with support from a trained research assistant (RA) who will be blinded to group allocation.

**Baseline data collection.** After obtaining written informed consent, baseline data—including demographics and all primary and secondary outcomes—will be collected. During baseline, an RA will provide in-person assistance to participants who experience any difficulty using the online platform.

**Post-intervention data collection.** The RA will contact and remind participants in both groups via WeChat, telephone, and/or email to complete post-intervention assessments at the designated time points. At T1, participants in the intervention group will complete questionnaires for all primary and secondary outcomes and an intervention satisfaction form within one week after completing all sessions. During the same period, participants in the control group will complete the same set of outcome questionnaires (without the satisfaction form). At T2 (six months post-intervention), the RA will contact/remind participants in both groups to complete follow-up assessments for all primary and secondary outcomes. At all three

time points, the RA will be available via WeChat and telephone to assist participants who encounter difficulties during data collection. The RA will review submitted questionnaires on the survey platform immediately after submission and will contact participants to complete any missing items when needed.

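### The protocol calls the data-collecting assistant blinded and says envelopes conceal allocation from parents, but a T1 form given to one arm reveals the arm and parents, who report every outcome, know theirs

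*Protocol*

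**What the plan says.** Protocol section 5.2.7 (Randomization and concealment) states: "Group allocation will be concealed from outcome assessors, rehabilitation school teachers, parents, and children using sequentially numbered, opaque, sealed envelopes". The sequence is held by an assistant who takes no part in recruitment, delivery or outcome assessment.

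Section 5.2.11 (Data collection procedure) makes the only explicit blinding claim. All quantitative data go through one online survey platform, "with support from a trained research assistant (RA) who will be blinded to group allocation". At T1, "participants in the intervention group will complete questionnaires for all primary and secondary outcomes and an intervention satisfaction form", while "participants in the control group will complete the same set of outcome questionnaires (without the satisfaction form"). The section then gives the RA a further duty: "The RA will review submitted questionnaires on the survey platform immediately after submission and will contact participants to complete any missing items when needed". The RA also sends the reminders at T1 and T2 and is on call for difficulties at every time point.

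On what parents experience, section 5.2.8 says that "parents in the intervention group will receive eight weekly sessions (2 hours per session") on top of usual care, and section 5.2.9 says of the comparator: "Usual care services will not include structured ACT content or the manualized WHO-CST curriculum". Section 5.2.10 describes the PSI-SF, PHQ-9, GAD-7, Psy-Flex and PSOC as self-reported and the SDQ as rated by the parent.

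**The concern.** Two statements about who is unaware of allocation do not fit the procedures around them.

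The first concerns the RA. A form that exists in one arm only, seen by the person who is meant to be blinded, shows which arm the parent is in. That person then decides when and how to follow up incomplete questionnaires and makes the T2 contacts. Knowing the arm could make that follow-up differ between arms, even without intent.

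The second concerns parents. A reader of 5.2.7 could take it that those who supply the outcome data do not know their allocation. Every outcome, including the primary one and the child outcome, comes from the parent. A report that followed the protocol's text could describe outcome assessment as blinded when it is not.

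**Working it through.** The point is one of consistency, so the check sets the sections side by side. No figure in the plan depends on blinding. For completeness, the stated total reproduces: a two-sample t-test with d = 0.5, two-sided 5% and 80% power needs 64 per arm, and 2 × 64 / (1 − 0.169) = 154.03, against the stated 154. Nothing below changes it.

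**Parents**

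1. Under 5.2.6 and 5.2.14, parents read an information sheet, have the study procedures explained and give written consent before entering the trial.
2. Under 5.2.8 and 5.2.9, one arm attends eight 2-hour group sessions with a workbook and homework; the other has usual care without that content. Under 5.2.14, control parents are offered the programme after the six-month data are collected.
3. A parent therefore knows the arm once the programme starts. A sealed envelope cannot prevent this.
4. Under 5.2.10, parents complete all six of the six outcome scales. For every outcome, the person giving the rating is unblinded at T1 and T2.

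**The RA, by time point (5.2.11)**

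| Stage | What the RA sees or does | Can the RA tell the arm? |
|---|---|---|
| T0 | Collects baseline data; gives help with the platform | No; both arms complete the same material |
| T1, before submission | Sends reminders; available for difficulties | Not by this mechanism |
| T1, on review | Checks the submission at once; a satisfaction form is present in one arm only | Yes, if the form is on the platform that the RA reviews |
| T1, after review | Contacts parents about missing items | Yes, from the previous step |
| T2 | Reminds, assists, reviews, contacts | Yes, from T1 |

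A satisfaction form that is present identifies an intervention parent with certainty. Its absence points to a control parent, though an intervention parent might not return it.

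The T1 review step rests on one inference. Section 5.2.11 does not say outright that the satisfaction form is on the survey platform. It does place all quantitative data there, lists the form together with the T1 questionnaires, and names no other route or handler for it.

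**The case against.** **The 5.2.7 sentence may mean only concealment before assignment.** It stands under a heading on randomization and concealment, describes envelopes, and does not use the word blinded. Section 5.2.10 is open about the outcomes being self-reported or parent-rated. This has weight: on that reading the sentence is loosely worded rather than false. The reading fits poorly, however. The sentence names outcome assessors, parents and children but not the staff who recruit and enrol, from whom a sequence most needs to be hidden. It also does nothing for the explicit blinding statement in 5.2.11.

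**The form may be handled apart from the outcome questionnaires.** This is possible, since the text is silent. If so, the protocol should say it, because as written nothing keeps the form from the RA.

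**Unblinded parents cannot be avoided with a usual-care comparator.** This is correct, and the design is not criticised for it. The point is that the text should say so.

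A reader might also infer several stronger things that the documents do not support:

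- *That teachers are unblinded too.* Section 5.2.4 says of the first four sessions only that "the intervention were administrated face-to-face at the children's rehabilitation institutions". It does not say that teachers learn who attends, and teachers rate no outcome.
- *That the RA is already unblinded when helping parents answer at T1.* The mechanism operates on review, after submission. At baseline the help described is with using the platform, and no section has the RA guiding answers.
- *That a particular false-positive rate follows.* Any such figure needs an assumed reporting shift that the documents do not give. It would mostly describe bias from parents knowing their arm, which the changes below would not remove.

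**Conclusion.** The concern holds for the RA and for parents. The RA blinding stated in 5.2.11 does not hold from T1 review onward, on the natural reading that the satisfaction form is collected on the platform the RA reviews, and taking the RA in that section to be one role throughout. Baseline collection is unaffected. The statement in 5.2.7 cannot be true of parents after assignment, and they are the source of all six scales.

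In extent, parents' knowledge of their arm touches every outcome at both post-baseline time points. The RA problem reaches missing-item follow-up at T1 and all RA contact at T2. The size and direction of any resulting bias cannot be derived from the documents. The sample size and the planned GEE analysis are unchanged. The point should be corrected because the RA breach is avoidable and because the present wording invites a claim of blinded outcome assessment that the procedures do not deliver.

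**What to change.** 1. **Separate the satisfaction form (5.2.11).** Send it by its own link after the T1 outcomes have been submitted. Have it handled by existing staff other than the outcome RA, and keep it out of that RA's view. The assistant who holds the allocation sequence could do this: 5.2.7 keeps that person out of outcome assessment, but satisfaction is not among the outcomes listed in 5.2.10. If this is not done, withdraw the RA blinding claim for everything after T1 submission.

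2. **Reword 5.2.7.** State that the sequence is concealed until assignment, that parents are not blinded afterwards, and that all outcomes are reported by unblinded parents. Conclusions should then not claim blinded outcome assessment.

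The cost is a second survey link and a few sentences of text, with no extra staff. The downside is that slightly fewer satisfaction forms may come back. The first change protects the RA's blinding only; it does not remove bias from parents knowing their arm, which is why the second is also needed.

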#### **5.2.8 Intervention Group**

In addition to usual care, parents in the intervention group will receive eight weekly sessions (2 hours per session) of an Acceptance and Commitment Therapy (ACT)-based parenting program delivered by the research team. The program will be administered in a

blended group format (face to face and online), with approximately 6–8 participants per group. The curriculum will cover four domains: (1) emotional and stress management (ACT); (2) autism-specific parenting skills; (3) autism-related education; and (4) self-care.

To establish rapport between the facilitator and participants, Session 1 will be delivered face to face. Sessions 2–4 will also be delivered face to face because they include experiential exercises (e.g., role-playing, mindfulness practices) that support learning of complex techniques and concepts. Sessions 5–8 will be delivered via an online videoconferencing platform (Tencent Meeting). During the final four online sessions, parenting practices will be taught step by step using instructional parenting videos, and core ACT principles (e.g., self-as-context) will be introduced using animated metaphor videos. All videos will be drawn from trustworthy, validated sources recommended by the World Health Organization’s Caregiver Skills Training for Families of Children with Developmental Delays and Disabilities (WHO-CST) and/or ACT manuals. Parents will receive a workbook outlining core ACT principles, key parenting skills, and weekly homework. Participants will be able to access online mindfulness practice videos after class by scanning QR codes provided in the workbook. A session-by-session outline of the ACT program will be provided in Table 1.

### **5.2.9 Control Group**

Based on the government policy document titled “Management Measures for Designated Rehabilitation Service Institutions for Disabled Children and Youth in Shenzhen”, parents will receive usual care services from their children’s rehabilitation institutions delivered by institutional staff (rehabilitation therapists, special educators, social workers with standard

local credentials) as part of routine, year-round services. To minimize nonspecific influences, both groups will have access to institution-based staff with comparable professional credentials and opportunities for contact and information provision. Usual care services will comprise in-person group education (~1 to 2 hours/session) and outreach activity (~3 to 4 hours/activity) held at least twice annually, as well as ad hoc individual consultations (~15 to 30 minutes/visit) covering autism-related rehabilitation education, interpretation of government support policies, or education on parental/child psychological health, with crisis referral when indicated). Usual care services will not include structured ACT content or the manualized WHO-CST curriculum; any overlap will be limited to general psychoeducation without skills training or fidelity-monitored components.

#### **5.2.10 Measures**

The instruments that will be used for outcome measurement in the RCT are described below.

**Demographic questionnaire.** A demographic data form was created to gather baseline information about parents and their children with autism. This form included details such as age, sex, family socioeconomic status, education level, and employment status. Moreover, it recorded children's medical characteristics, including the diagnosis dates for autism, any other medical conditions, and types of medications used in relation to autism.

#### **Primary outcomes**

The *Chinese version of the Parenting Stress Index – Short Form (PSI-SF)* is a 15-item self-reported questionnaire measuring parental stress by rating on a 5-point Likert scale (1 –

“strongly disagree” to 5 – “strongly agree”). A higher score indicates a greater parental stress. This instrument was adopted from the original PSI-SF (36-item; and designed to measure three domains: parental distress (PD), parent-child dysfunctional interaction (PCDI), and difficult child (DC). The Cronbach’s  $\alpha$  of PSI-SF-15 was 0.87/0.86 (mother/father) for the total scale, 0.71/0.72, 0.82/0.78, and 0.79/0.78 for PD, PCDI, and DC, respectively, confirming its good internal consistency in Chinese parents. The three-factor model with five items each was confirmed by confirmatory factor analysis (CFA) with an acceptable model fit and good structure validity. No cut-off point for the Chinese version was reported.

#### **Secondary outcomes for parents**

The *Patient Health Questionnaire (PHQ-9)* is a nine-item self-reported questionnaire measuring depressive symptoms by rating on a 4-point Likert scale (0 – “Not at all” to 3 – “Nearly every day”). The higher scores indicate higher severity of depressive symptoms. The cut-off scores for this instrument were categorised as follows: mild depression (5-9), moderate depression (10-14), moderately severe depression (15-19), and severe depression ( $\geq 20$ ). The Chinese version of the PHQ-9 was validated in community adults and reported a good internal consistency reliability ( $\alpha = 0.86$ ) and a good one-factor structure (Kaiser–Meyer–Olkin = 0.89; the chi-square value of the Bartlett’s Test of Sphericity = 3453.80,  $p < .001$ ).

The *Generalised Anxiety Disorder-7 (GAD-7)* is a seven-item self-reported questionnaire measuring anxiety symptoms by rating on a 4-point Likert scale (0 – “Not at all” to 3 – “Nearly every day”). The higher scores indicate higher severity of anxiety disorders. The cutoff points of this instrument were categorised as follows: none/normal (0-4), mild anxiety (5-9), moderate

anxiety (10-14), and severe anxiety (15-21). The Chinese version of the GAD-7 was validated in outpatients from traditional Chinese internal departments and indicated an excellent internal consistency reliability ( $\alpha = 0.91$ ) and an adequate one-factor model fit (area under the curve=0.80).

The *Psy-Flex* is a six-item self-reported questionnaire measuring psychological flexibility by rating on a 5-point Likert scale (5 – “very often” to 1 – “very rarely”). A higher score indicates a greater psychological flexibility. The Cronbach’s  $\alpha$  of the original version was 0.91 for the total sample and ranged from 0.78 to 0.97 for subsamples, representing a good internal consistency of the Psy-Flex in both clinical and non-clinical adults. The reliability and validity of the Chinese version of the Psy-Flex were assessed in a sample of 248 Chinese parents of children with autism. The results demonstrated adequate internal consistency (Cronbach’s  $\alpha = 0.84$ ) and test-retest stability (weighted kappa = 0.88), along with a well-fitting one-factor structure for the Psy-Flex-C ( $\chi^2/df = 1.62$ ,  $p = 0.125$ , RMSEA = 0.05, GFI = 0.99, CFI = 0.99, TLI = 0.98, SRMR = 0.02).

The *Parenting Sense of Competence Scale (PSOC)* is a 17-item self-reported questionnaire assessing parenting competence by rating on a 6-point Likert scale (1 – “strongly disagree” to 6 – “strongly agree”). This instrument was categorised into two subscales of parenting, including the efficacy subscale (eight-item; test parents’ perceived self-efficacy in the parenting role) and the satisfaction subscale (nine-item; examine parents’ satisfaction and comfort with the parenting role). Higher scores indicate a higher sense of parenting competence in parenting. The Chinese version of the SDQ has been tested and validated in Chinese parents,

teachers, and students (aged 6–15 years), including those with and without ADHD. Internal consistency for most factors across the parent-, teacher-, and self-report versions was moderate to high (Cronbach's  $\alpha = 0.55$ – $0.86$ ), with the exception of a lower  $\alpha$  for the 'Peer Problems' factor in the self-report version ( $\alpha = 0.40$ ). Four-week test–retest reliability was satisfactory (intraclass correlations =  $0.67$ – $0.91$ ).

